## Criteria for discontinuing or modifying allocated interventions {11b}

### During intervention

Several measures will be taken in order to protect the participants’, child’s parent(s), or guardian(s) wellbeing and identity as follows. Firstly, according to the exclusion criteria, participants suffering from medical conditions or other serious health conditions that are incompatible with undertaking an exercise regimen will not be considered for inclusion and will immediately be referred to healthcare professionals. Secondly, if participants’ physical or emotional condition deteriorates during the trial, they will immediately be excluded from the trial and will similarly be referred to appropriate practitioners. Finally, participants will be informed that participation is voluntary and that they may discontinue the intervention at their free will. Any adverse events and other unintended effects of trial interventions or trial conduct will be addressed by the project coordinator ([name]).

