### Exercise group

If allocated to the intervention group, participants will undergo a 12-week exercise intervention utilizing a gamified online platform designed for children to engage in physical activity with their families at home or in outdoor spaces (Fig. 2), followed by a 12-week follow-up period. The platform features pre-recorded video exercises and is designed to be followed by normal daily routines. Participants are required to log in and complete the exercises 2 times per week, with a different session available Monday to Wednesday and repeated from Thursday to Sunday. The program consists of various phases, including bodyweight strength training, cardiovascular exercises, and color-coded exercises, with varying exercises and repetition counts or duration from week to week. Each session includes a warm-up/activation phase, a training phase, and a cool down phase. The warm-up phase is 3 min of light intensity continuous training, the training phase is 10–26 min with 6–12 repetitions, 20–40 s of work, and 10–20 s of recovery, and the cool down phase is 3 min of static and dynamic exercises. The exercises will change each week, increasing in length and intensity. The program will be supervised by the child’s parent(s) or guardian(s).

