#### Quality of life

Data on the quality of life and self-regulation abilities of the children will be assessed using the KIDDY-KINDLR and the Child Self-Regulation & Behaviour Questionnaire (CSBQ) [32]. The KIDDY-KINDLR will assess physical and psychological well-being, self-esteem, family, friends, and school. The following six dimensions of children’s quality of life will be assessed through questions in a standardized questionnaire: physical well-being, psychological well-being, self-esteem, family, friends, and school. Participants will be asked about their experiences in each of these areas over the past week. Questions may include the following: “Have you felt sick?” for physical well-being, “Have you laughed and had lots of fun?” for psychological well-being, “Are you proud of yourself?” for self-esteem, “Have you gotten along with your parents?” for family, “Have you played with your friends?” for friends, and “Have you been able to do your homework well?” for school.

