## Assignment of interventions: blinding

### Who will be blinded {17a}

The assignment password will be kept in a confidential file in the Navarrabiomed center and will be opened at the end of the study’s analyses. To ensure masking, an alpha-numerical code will be assigned to each study group. This code will be delivered to the associated researcher and will not be revealed to the investigators in charge of processing the data until the analysis of the coded interventions is completed. Additionally, the researchers from the Navarrabiomed center will be responsible for preparing reports for the participants’ safety committee to verify the progress of the study. Following the conclusion of the baseline examination, the appropriate envelope will be opened by a study researcher, and the participants will be informed about their group allocation. Assessors of outcomes will be blinded to patient data, including allocation at baseline and follow-up. Blinding will be used for all specialized analyses. Owing to the nature of the study, patients cannot be blinded to the exercise training modality.

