## Statistical methods

### Statistical methods for primary and secondary outcomes {20a}

The study will adhere to the intention-to-treat principle and use the baseline observation carried forward imputation method, where missing data will be replaced by baseline values [39]. The final analysis population will be described and any differences from the enrolled population will be reported. Participants who drop out of the study may still be included in the analysis, although their data will provide less information and lower the estimated effects variance. Adherence will be measured as the number of completed sessions divided by the total number of sessions, expressed as a percentage. The first step of the analysis will be to calculate descriptive statistics for the overall sample and between groups. Since this is an experimental design with primary and secondary outcomes measured at three timepoints - baseline (t0 = week 0), post-intervention (t1 = week 12), and after a 12-week follow-up period (t2 = week 24) - for the two study groups (exercise and routine care), a comparative analysis between the measurements will determine the differences. A linear mixed model with repeated observations will be used for these comparisons, when appropriate, for each dependent variable. Subsequently, multivariate analysis will be carried out, and the autocorrelation between repeated measures will be taken into account. We will use longitudinal analysis methods, such as a generalized estimating equation approach, to control the differences among measurements at baseline and to incorporate incomplete observations into this analysis. Pearson correlations will be calculated between the maximal values of the primary and secondary outcomes. All analyses will be 2-sided and a significance level of *α* ≤ 0.05 will be used for the primary analysis.

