### Methods in analysis to handle protocol non-adherence and any statistical methods to handle missing data {20c}

The potential effects of missing data will be explored under various models for nonignorable missing data mechanisms and through multiple imputation models under ignorable missing data assumptions [40].

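### A child who deteriorates is excluded from the trial, not only from the exercise, so worsening not yet recorded is lost, mainly from the quality-of-life and behaviour scales

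*Protocol article*

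**What the plan says.** Under Criteria for discontinuing or modifying allocated interventions {11b}, During intervention, the rule for a child whose "physical or emotional condition deteriorates during the trial, they will immediately be excluded from the trial" is paired with referral to a practitioner. The next sentence words voluntary stopping differently: families are told that "they may discontinue the intervention at their free will". One is an exit from the study, the other an exit from the exercise.

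Statistical methods {20a} adopts intention-to-treat with baseline observation carried forward: "missing data will be replaced by baseline values". It adds that "Participants who drop out of the study may still be included in the analysis", and it also names a linear mixed model and generalised estimating equations that can use incomplete observations. Section {20c} will explore missing data under "various models for nonignorable missing data mechanisms and through multiple imputation models under ignorable missing data assumptions".

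Two other rules remove children at study level. Intervention descriptions {11a} ends participation for those below 70% of training (17 of 24 sessions). Routine care group repeats a similar rule for children who do not carry out their training. Nothing in the article provides for a week 12 or week 24 assessment after any of these removals.

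The outcomes closest to the trigger are secondary. "The KIDDY-KINDLR will assess physical and psychological well-being, self-esteem, family, friends, and school"; the CSBQ, and the SDQ for children over 5, cover emotional and behavioural problems.

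**The concern.** The trigger for removal is a worsening in what the well-being and behaviour scales measure. The missing values are therefore missing because they would have been poor. Carrying baseline forward gives such a child a change of exactly zero. Leaving the child out removes the worsening altogether. Either way the arm mean looks better than it was.

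Mental and behavioural health is part of the stated objective, so these scales matter even though they are secondary. The loss is also avoidable. Protecting the child requires stopping the exercise and referring; it does not require stopping a questionnaire that a parent fills in online.

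**Working it through.** The protocol states no rate of deterioration, no threshold and no link between the clinical judgement and the questionnaire scores, so there is no figure of its own to reproduce. What follows is a set of assumed scenarios.

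**Inputs from the protocol.** About 40 children per arm (Fig. 1; the sample size section says 42) and a 10% dropout allowance (Sample size {14}).

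**Assumed.** Outcome change D = μ + e, with e ~ N(0,1), so change has SD 1 and negative means worse; μ = 0 in control. The trigger is T = μ + r·e + √(1−r²)·z, with z ~ N(0,1) independent, so r is the correlation between trigger and outcome. A child with T below cut-off c is noticed and excluded with probability d, before the outcome is recorded.

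**Formulas.** With p = Φ(c−μ) and S = μp − r·φ(c−μ):
- baseline carried forward: arm mean = μ − dS
- left out: arm mean = (μ − dS)/(1 − dp)
- effect = exercise minus control
- standard error of a difference = √(2/40) = 0.224 SD (0.218 with 42)

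**Worked case: equal detection (d = 1), true effect −0.30, c = −1.5, r = 1.**
- Exercise: p = Φ(−1.2) = 0.115; S = −0.30 × 0.115 − 0.194 = −0.229; mean = −0.30 + 0.229 = −0.071
- Control: p = Φ(−1.5) = 0.067; S = −0.130; mean = +0.130
- Effect = −0.071 − 0.130 = −0.201

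The bias is 0.099 SD, or 0.099/0.224 = 0.44 standard errors. Excluded: 4.6 of 40 and 2.7 of 40, or 9.1% overall.

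**Equal detection, true effect −0.30**

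| c | Excluded | r | Baseline carried forward | Left out |
|---|---|---|---|---|
| −1.5 | 9.1% | 1 | −0.201 | −0.219 |
| −1.5 | 9.1% | 0.5 | −0.233 | −0.260 |
| −2 | 3.4% | 1 | −0.247 | −0.257 |
| −2 | 3.4% | 0.5 | −0.267 | −0.278 |

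With equal detection and a true effect of 0, both arms shift alike and the difference stays 0.

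**Unequal detection (all noticed in exercise, half in control), true effect 0**

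| c | Excluded | r | Baseline carried forward | Left out |
|---|---|---|---|---|
| −1 | 11.9% | 1 | +0.121 | +0.156 |
| −1 | 11.9% | 0.5 | +0.060 | +0.078 |
| −1.5 | 5.0% | 1 | +0.065 | +0.072 |
| −1.5 | 5.0% | 0.5 | +0.032 | +0.036 |
| −2 | 1.7% | 1 | +0.027 | +0.028 |
| −2 | 1.7% | 0.5 | +0.013 | +0.014 |

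**Unequal detection, true effect −0.30, baseline carried forward.** At c = −1.5 the estimate is −0.136 (r = 1) or −0.201 (r = 0.5); at c = −2 it is −0.220 or −0.253.

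**Against the standard error.** Most biases are below half of 0.224. The exceptions need r = 1 and unequal detection: 0.121/0.224 = 0.54, 0.156/0.224 = 0.70, and (0.300 − 0.136)/0.224 = 0.73. The first two also exclude 11.9%, above the dropout allowance. A cut-off of −1 with a true harm is not tabulated, because it would exclude (0.242 + 0.5 × 0.159)/2 = 16% or more.

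**Would another analysis repair it?** In a separate simulation (baseline to follow-up correlation 0.6, true difference 0), the worst 10% of changes were removed from exercise and none from control. The false benefit was 0.157 SD with baseline carried forward, 0.174 with children left out and 0.148 with regression under missing at random. Only measuring the children brings it to zero.

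**Why not activity, fitness or motor scores?** Assume an average gain of 1 SD. Among children whose trigger lies more than 1.5 SD below average, the mean of e is −r × 0.1295/0.0668 = −1.94r. Their mean true change is 1 − 1.94 = −0.94 (r = 1), +0.03 (r = 0.5) or +0.42 (r = 0.3). Setting them to baseline can err in either direction.

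**The case against.** The wording may be loose. The sentence sits under a heading about interventions, the analysis is declared intention-to-treat, and a condensed article may leave follow-up procedures to the operating manual it mentions. That stands as a caution. But the contrast with the next sentence, and the study-level wording of the adherence rules, favour the literal reading.

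The left-out branch is the weaker one. It reads the sentence on dropouts as permission to omit them, while the same section commits to intention-to-treat. Baseline carried forward is therefore the main case.

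The planned nonignorable models are the right class of sensitivity analysis, and the plan will report how the analysed and enrolled populations differ. Both help, but neither recovers a value that was never measured.

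The scenarios are assumptions. Taking r = 1 equates a clinical judgement with a questionnaire score, and 9.1% excluded would use nearly the whole dropout allowance on deterioration alone, in a trial that expects minimal risk. This is why the size is given as a range and called probably small.

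A reader might infer that the rule favours exercise. The documents do not support that. Unequal detection is plausible, since "patients cannot be blinded to the exercise training modality" and exercise-arm parents supervise the sessions ("Participants are required to log in and complete the exercises 2 times per week"), but it is not stated, and the sign reverses if controls are watched more closely.

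**Conclusion.** The point holds, at low priority. Followed as written, the plan stops measuring a child because the child has worsened, then scores that child as unchanged at the visits still to come. It rests on the literal reading of the exclusion sentence and on the absence of any stated assessment afterwards.

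The loss is of worsening after the last recorded visit. It would be too strong to say that all worsening disappears: a child excluded after week 12 keeps the week 12 value. It would also be too strong to infer bias in daily moderate-to-vigorous activity, where the direction is uncertain, or to say that harms go unreported, since adverse-event reporting is a separate channel.

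On the KIDDY-KINDLR, CSBQ and SDQ, a true harm of 0.30 SD would be estimated at 0.20 to 0.27 SD under equal detection and baseline carried forward. A true null moves only if detection or removal differs between arms. Biases are mostly below half a standard error and reach 0.5 to 0.7 only at r = 1 with unequal detection. All rates are assumed.

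**What to change.** - **Section {11b}:** reword so that deterioration stops the intervention, with referral as now, but not trial follow-up.
- **Intervention descriptions {11a} and Routine care group:** state that missing sessions, at least for this reason, ends the training and not the week 12 and week 24 assessments, in both arms alike. Without this, an exercise-arm child who stops before session 17 would still be removed while a deteriorated control, who has no sessions to miss, stays. That would create unequal loss.
- **Follow-up:** invite these families to both assessments, at minimum the parent-completed questionnaires. The CSBQ already goes through an online form and needs no visit.
- **Analysis:** use observed values in the allocated arm. For values still missing, use the planned mixed model on observed data instead of baseline imputation, with the nonignorable models of {20c} as sensitivity analyses. The mixed model alone does not remove the bias; measuring the children does.
- **Reporting:** give numbers and reasons by arm.
- **Consent {26b}:** extend the data-use question, which now covers families who choose to withdraw, to this case.

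The cost is an ethics amendment, one consent line and a few extra questionnaires or visits from consenting families. The clinical decision and the referral do not change.

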### Strategies to improve adherence to interventions {11c}

The “3, 2, 1 Move on Study” research staff received training regarding Good Clinical Practice (GCP), the study protocol (including subsequent amendments), intervention, recruitment strategies, data collection using an electronic database, and inspection. A manual detailing the standard operating procedures (SOP) for the trial (including subsequent updates) will be available to all members of the research team. These will ensure ongoing protocol adherence and consistency. The information provided ensures all participants receive identical verbal and written information and instructions regarding the study. Regular assessment of treatment fidelity by the clinical trial coordinator (CTC) focuses on data integrity, the trial compliance, and its application.

### Relevant concomitant care permitted or prohibited during the trial {11d}

Routine care according to hospital procedures and informed by state governance and international standards (12) continues throughout the trial for all participants.

### Provisions for post-trial care {30}

Routine care according to hospital procedures and informed by state governance and international standards (12) is provided within the public health service in Navarra, Pamplona (Spain).

There is no anticipated harm and compensation for trial participation. There will be no provisions for post-trial care.

### Patient and public involvement (PPI)

To incorporate PPI, we will establish a collaboration with a local pediatric patient advocacy group and engage with parents, caregivers, and children themselves. Through focus group discussions, surveys, and one-on-one interviews, we sought their insights on the study objectives, exercise interventions, outcome measures, and participant experience.

## Outcomes {12}

### Primary outcome

The primary outcome will be mean minutes of moderate-to-vigorous physical activity (MVPA) per day assessed using GENEActiv accelerometers. The study will be able to detect a difference in the mean daily MVPA between intervention and routine care of ± 5 min at follow-up.

### Secondary outcomes

#### Anthropometric and body composition assessment

Participants will undergo testing while wearing minimal clothing and without footwear. Anthropometric measurements will be taken to determine weight, height (Seca 213, Seca Ltd, Birmingham, UK), waist circumference (WC), and body mass index (BMI). These values will be compared against WHO standards [25]. Additionally, body composition will be evaluated to determine the percentage of fat and lean mass, using bioelectrical impedance analysis (Tanita DC430 MA, Tanita Corporation, Tokyo, Japan), and ultrasound scans from the femoral rectus for muscle thickness, subcutaneous adipose tissue (SAT), and area of the muscle of interest. In addition, the medical team involved in the project will assess children’s systolic and diastolic blood pressure and triceps skinfold thickness.

#### Health-related physical fitness

Data on specific physical fitness related to health will be obtained with the 20-m shuttle run test (adapted to the children’s age) to assess aerobic capacity, the handgrip strength test (Grip Strength Dynamometer T.K.K. 5001 Grip A) and standing long jump test to assess musculoskeletal capacity, the 4 × 10-m speed and agility test to assess motor capacity, and the sit and reach flexibility test to measure trunk flexibility.

In Spain, the PREFIT battery is being administered [26] to provide national physical fitness reference values that interpret the results of the physical fitness assessment. Physical fitness, especially cardiorespiratory capacity and muscular strength, is a good indicator of health in children and adolescents [27]. A review of 32 studies found that the 20-m shuttle run test, the handgrip strength test, the standing  long jump test, the 4 × 10-m shuttle run agility test, and the BMI, skinfold, and waist circumference tests are reliable field-based fitness tests for children and adolescents [28].

#### Physical activity and sedentary habits

Data on physical activity levels will be collected using accelerometry over 7 consecutive days on the non-dominant wrist to record physical activity and sleep information (GENEActiv), using the YAP-S (Youth Activity Profile-Spain) questionnaire adapted for preschoolers to evaluate physical activity and sedentary habits, and the GPAQ (Global Physical Activity Questionnaire) to evaluate the parent’s physical activity.

#### Basic motor competencies (BMC)

The assessment of basic motor competencies (BMC) in preschoolers aged 4 to 6 years was conducted using the MOBAK KG test instrument [29]. The test consists of 8 items, divided into 4 object movement (OM) competencies and 4 self-movement (SM) qualifications. OM tasks include throwing, catching, bouncing, and dribbling, while SM tasks include balancing, rolling, jumping, and running. Children can earn a maximum of 8 points per area (4 items, 2 points each), totaling 16 points.

Before performing the tasks, participants were not given any prior attempts to practice. For the “throwing” and “catching” tasks, participants had six attempts to complete the task. Scoring was based on the number of successful attempts, with 0–2 attempts scoring 0 points, 3–4 attempts scoring 1 point, and 5–6 attempts scoring 2 points. In the “bouncing,” “dribbling,” “balancing,” “rolling,” “jumping,” and “running” tasks, participants had two attempts to complete each task. These items were scored dichotomously (0 = failed; 1 = passed), with the number of successful attempts recorded. A score of 0 points was awarded for never passed, 1 point for once passed, and 2 points for passed twice.

BMC play a vital role in child development and are a primary focus of physical education. Children aged 3–6 years are at a crucial stage in improving their motor skills, as everything they do involves motor actions such as posture, movement, exploration, social interaction, and object manipulation [30]. A validated and simple tool for assessing BMC is the MOBAK KG test, which evaluates two competence areas: object movement (OM) and self-movement (SM) [31].

#### Executive function

Participants will be assessed for their executive function using digital test on iPads, administered by research assistants. These tests will include games from the “Early Tools” (Years Toolbox YET-2017) such as “[name]” and “Not this” to measure memory, “Card sorting” to evaluate cognitive flexibility, and “Go/No-Go” to assess inhibitory capacity.

#### Quality of life

Data on the quality of life and self-regulation abilities of the children will be assessed using the KIDDY-KINDLR and the Child Self-Regulation & Behaviour Questionnaire (CSBQ) [32]. The KIDDY-KINDLR will assess physical and psychological well-being, self-esteem, family, friends, and school. The following six dimensions of children’s quality of life will be assessed through questions in a standardized questionnaire: physical well-being, psychological well-being, self-esteem, family, friends, and school. Participants will be asked about their experiences in each of these areas over the past week. Questions may include the following: “Have you felt sick?” for physical well-being, “Have you laughed and had lots of fun?” for psychological well-being, “Are you proud of yourself?” for self-esteem, “Have you gotten along with your parents?” for family, “Have you played with your friends?” for friends, and “Have you been able to do your homework well?” for school.

